## Abstract

*Background and Objectives:* In anticoagulated atrial fibrillation (AF) patients, the validity of models recommended for the stratification of the risk ratio between benefits and hemorrhage risk is limited. Cerebral small vessel disease (SVD) represents the pathologic substrate for primary intracerebral hemorrhage and ischemic stroke. We hypothesize that biological markers—both circulating and imaging-based—and their possible interaction, might improve the prediction of bleeding risk in AF patients under treatment with any type of oral anticoagulant. *Materials and*
*Methods*: The Strat-AF study is an observational, prospective, single-center hospital-based study enrolling patients with AF, aged 65 years or older, and with no contraindications to magnetic resonance imaging (MRI), referring to Center of Thrombosis outpatient clinic of our University Hospital for the management of oral anticoagulation therapy. Recruited patients are evaluated by means of a comprehensive protocol, with clinical, cerebral MRI, and circulating biomarkers assessment at baseline and after 18 months. The main outcome is SVD progression—particularly microbleeds—as a selective surrogate marker of hemorrhagic complication. Stroke occurrence (ischemic or hemorrhagic) and the progression of functional, cognitive, and motor status will be evaluated as secondary outcomes. Circulating biomarkers may further improve predictive potentials. *Results*: Starting from September 2017, 194 patients (mean age 78.1 ± 6.7, range 65–97; 61% males) were enrolled. The type of AF was paroxysmal in 93 patients (48%), and persistent or permanent in the remaining patients. Concerning the type of oral anticoagulant, 57 patients (29%) were on vitamin K antagonists, and 137 (71%) were on direct oral anticoagulants. Follow-up clinical evaluation and brain MRI are ongoing. *Conclusions*: The Strat-AF study may be an essential step towards the exploration of the role of a combined clinical biomarker or multiple biomarker models in predicting stroke risk in AF, and might sustain the incorporation of such new markers in the existing stroke prediction schemes by the demonstration of a greater incremental value in predicting stroke risk and improvement in clinical outcomes in a cost-effective fashion.

## 1. Introduction

Thromboprophylaxis with oral anticoagulation effectively reduces stroke risk in patients with atrial fibrillation (AF). Benefits must be balanced against the risk of bleeding, with intracranial hemorrhage being the most feared. Stroke and bleeding risk stratification schemes are aimed at identifying patients who may benefit most from different types of oral anticoagulation (vitamin K antagonists vs. direct oral anticoagulants). Currently, such schemes (e.g., CHADS2VASC2 and HASBLED scores) rely only on clinical information, the validity of which remains controversial and needs to be improved. In AF patients, advanced imaging technology such as magnetic resonance imaging (MRI), has led to the increased detection of asymptomatic brain changes, mainly those related to small vessel disease (SVD), which is the pathologic substrate for primary intracerebral hemorrhage (ICH) [1,2,3,4,5,6]. These changes have also been proven to strongly predict stroke risk [2,5]. Such imaging findings, obtained both at baseline and in terms of lesion progression over time, could be used as additional markers for risk stratification [3,7]. Furthermore, markers of coagulation activation, including prothrombin fragment 1+2, thrombin–antithrombin complex, D-dimer, time in therapeutic range for warfarin, and drug dosage for new anticoagulants, may be also studied as cofactors. Preliminary data suggest that circulating biomarkers of endothelial dysfunction, hypercoagulable state, and inflammation may further enhance risk prediction [4].

The validity of the currently recommended models for the stratification of risk ratio between benefits and hemorrhagic risk in anticoagulated AF patients is limited. These models do not specifically take intracranial hemorrhage into account, which is indeed the most severe hemorrhagic complication [8]. Our hypothesis is that biological markers—both circulating and imaging-based, and their possible interaction—might improve the prediction of bleeding risk in AF patients treated with any type of oral anticoagulant. Neuroimaging biomarkers of SVD—particularly microbleeds—may serve as a selective surrogate marker of hemorrhagic complications. Circulating biomarkers assessed together with imaging may further improve predictive potentials.

In this scenario, we set up the prospective observational Strat-AF study, primarily aimed at investigating circulating biomarkers and MRI markers (baseline and progression) of SVD as surrogate markers for the prediction of cerebral bleeding in a cohort of patients with AF on oral anticoagulants. Secondary outcomes included stroke occurrence (either ischemic or hemorrhagic) and the progression of functional, cognitive, and motor status.

## 2. Materials and Methods

Stratification of Cerebral Bleeding Risk in AF, Strat-AF, Strat-AF is an observational, prospective, single-center hospital-based study enrolling patients with AF, referring to the Center of Thrombosis outpatient clinic of our University Hospital for the management of oral anticoagulation therapy.

### 2.1. Inclusion Criteria

Diagnosis of AF and ongoing oral anticoagulation therapy;Aged ≥ 65 years;No contraindications to MRI.

### 2.2. Exclusion Criteria

Inability or refusal to undergo cerebral MRI;Inability to give an informed consent.

All subjects gave their informed consent for inclusion before they participated in the study. The study was conducted in accordance with the Declaration of Helsinki, and the protocol was approved by the Ethics Committee of the Careggi University Hospital (Project identification code 16RFAP, approved on March 2017). 

Sample size was estimated based on a feasibility criterion (i.e., the real flow of patients to the Thrombosis outpatient clinic of Careggi Hospital). Yearly, approximately 600 patients with AF on oral anticoagulation refer to the outpatient clinic. Considering a foreseeable rate of ineligible patients and refusals, we originally estimated to contact approximately 300 patients in one year fulfilling the inclusion criteria. Starting from September 2017, consecutive eligible patients were invited to participate in the study. The initial foreseen period for enrollment was 12 months, but in order to augment the number of included patients, we extended the enrollment period to 18 months.

### 2.3. Clinical Assessment

All enrolled patients were assessed at baseline by means of a standard clinical/functional protocol collecting information on vascular risk factors (particularly hypertension and diabetes), dietary habits, previous cerebrovascular events, general neurological and functional status, cognitive performances, mood and gait disorders, and general neurological examination. 

In detail, clinical data were collected about social and medical history; a standard cardiovascular and neurological examination, including office blood pressure measurement, were performed. Functional status was assessed using the Activities of Daily Living scale and the Instrumental Activities of Daily Living scale [9,10]; mood assessment using the Geriatric Depression Scale [11]; motor performance using the Short Physical Performance Battery [12]; daytime sleepiness using the Epworth Sleepiness Scale [13]; and quality of life using the EuroQol Visual Analog Scale [14]. Dietary habits were assessed by means of the questionnaire on the adherence to the Mediterranean diet [15].

A comprehensive multi-domain cognitive assessment, including global functioning, orientation, memory, attention, executive functions, language, speed, and motor control was administered to each included patient. 

The cognitive domains assessed by means of the extensive battery of tests were as follows:Global cognitive efficiency, by means of the Montreal Cognitive Assessment (MoCA): it is a 10-minute cognitive screening tool created to detect mild cognitive impairment (MCI), suggested from the harmonization standards of the National Institute of Neurological Disorders and Stroke—Canadian Stroke Network (NINDS-CSN) and thought to be specifically sensitive to frontal, attention, and executive deficits [16,17,18]. It covers eight cognitive domains: short-term and delayed verbal memory; visuospatial abilities; executive functions; attention; concentration; working memory; language; and orientation (score range 0–30)Verbal memory, by means of the Rey Auditory-Verbal Learning Test (RAVLT) and the Short Story Recall Test [19,20]. The RAVLT and Short Story Recall Test measure several components of verbal memory, such as immediate free recall, verbal learning, and retention of information after a certain period of time. Two scores are obtained from the RAVLT: immediate free recall (range 0–75) and delayed free recall (range 0–15). The Short Story Recall Test has a total score obtained by the mean number of elements correctly remembered on the immediate and delayed recalls (score range 0–28).Attention, by means of the Visual Search test [21]. This is a number cancellation task that requires visual selectivity at fast speed, and assesses the capacity for sustained attention and accuracy of visual scanning (score range 0–60). The Colour Word Stroop test was also used [22]. It is a measure of concentration effectiveness and deals with response inhibition and selective attention. The activity required by this test is a selective processing of only one visual feature while continuously blocking out the processing of others. The execution time and the errors committed are recorded.Language, by means of:
Semantic verbal fluency test: a test allowing the semantic evaluation of lexical access [23]. Three categories were tested: car brands, fruits, and animals. The total score was given by the sum of the number of words produced for each category in one minute.Sentence construction test: a test used to evaluate the verbal ability to construct a meaningful sentence starting from a set of two or three words (score range 0–25) [19]. 

All raw test scores were demographically corrected according to Italian population normative data, and adjusted scores were then recoded as normal, borderline, or abnormal according to equivalent scores (ES) methodology [24]. ES methodology is a non-parametric norming method based on percentiles and is independent from the distribution form. ES is an ordinal 5-point scale (ranging from 0 to 4), and the main point of ES methodology is to fix the outer tolerance limit of the left queue of the adjusted scores so that it is possible to assess, with a known risk of error (<5%), the cut-off splitting the bottom 5% of the population and representing pathological performance (ES = 0). At the other end of the scale, ES = 4 indicates an optimal performance (equal to or better than the median). ES = 1 indicates a borderline performance (an adjusted score between the outer and inner confidence limits for the fifth centile of the normal population), while the remaining ES scores of 2 and 3 represent normal performances.

The diagnosis of MCI requires at least one altered score (ES = 0) plus one borderline score (ES = 1) in any cognitive test included in the neuropsychological battery.

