### 2.7. Secondary Endpoints 

Secondary endpoints will be:Stroke occurrence (ischemic or hemorrhagic).Considering data from medical history and available laboratory and imaging exams, new major cerebrovascular events will be recorded as ischemic or hemorrhagic strokes. Ischemic strokes will be further categorized in subtypes according to the TOAST classification system [27]. Hemorrhagic strokes will be classified according to lesion type and location.Progression of global functioning, cognitive, and motor performances.Progression in cognitive status will be determined by the occurrence of a diagnosis of MCI or dementia, and defined according to performances on the comprehensive neuropsychological test battery (evaluated as normal or abnormal by means of national normative data), and functional status.The change in global functional status will be based on the Activities of Daily Living and Instrumental Activities of Daily Living scales, and the worsened condition will be defined as the loss of at least one item (i.e., the patient became dependent for an item function that was preserved at baseline evaluation).Motor status will be evaluated by means of the Short Physical Performance Battery. Based on the total score (range 0–12), at each visit individuals will be categorized as having normal (SPPB ≥ 11) or impaired mobility (SPPB ≤ 10), and variations in performance categories over time (baseline vs. 18 months) will be evaluated for each patient.

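### As written, the MCI rule leaves out patients with two or more pathological scores and no borderline score, and section 2.7 describes a coding that cannot apply the rule

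*Protocol article*

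**What the plan says.** Section 2.3 (Clinical Assessment) of the protocol article turns each neuropsychological score into an equivalent score: "ES is an ordinal 5-point scale (ranging from 0 to 4"). The lowest value is defined by "the cut-off splitting the bottom 5% of the population and representing pathological performance (ES = 0"). The next value is a separate and better category: "ES = 1 indicates a borderline performance (an adjusted score between the outer and inner confidence limits for the fifth centile" of the normal population). The scores are then grouped at three levels: "adjusted scores were then recoded as normal, borderline, or abnormal according to equivalent scores (ES) methodology".

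The diagnostic rule follows: "The diagnosis of MCI requires at least one altered score (ES = 0) plus one borderline score (ES = 1"), counted over any tests in the battery.

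Section 2.7 (Secondary Endpoints) makes this diagnosis an endpoint: "Progression in cognitive status will be determined by the occurrence of a diagnosis of MCI or dementia". It says that the diagnosis rests on the test battery, with performance "evaluated as normal or abnormal by means of national normative data), and functional status".

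**The concern.** On a scale where 0 is worse than 1, a severity rule should keep holding when a score gets worse. This one does not. It asks for a score of exactly 1 beside the 0, so a profile with more pathological scores can fail where a milder profile passes.

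The cognitive secondary endpoint is at stake, in two ways. A patient with several pathological scores and no borderline score at baseline is filed as non-MCI. A patient who is normal at baseline and has that profile at 18 months is not counted as having progressed, unless dementia is diagnosed.

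The two sections also describe the coding differently. A two-level coding has no borderline level, so it cannot be used to apply a rule that asks for ES = 1.

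**Working it through.** The protocol article gives no rate or power figure on this point, so there is no stated number to reproduce. The check is of logic first and frequency second.

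**1. The rule as a formula.** Let n0 be a patient's number of scores with ES = 0 and n1 the number with ES = 1.

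- Rule as written (section 2.3): n0 ≥ 1 and n1 ≥ 1.
- Minimum-severity reading: n0 ≥ 1 and n0 + n1 ≥ 2, i.e. one ES = 0 plus a further score of 0 or 1.
- Patients who meet the second but not the first: n0 ≥ 2 and n1 = 0.

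**2. Profiles (all other scores normal).**

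| Scores | As written | Minimum severity |
|---|---|---|
| 0, 1 | MCI | MCI |
| 0, 0 | not MCI | MCI |
| 0, 0, 0 | not MCI | MCI |
| 0, 0, 1 | MCI | MCI |
| all scores 0 | not MCI | MCI |

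This step needs no assumption about patients.

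**3. A case that can be checked by hand.** Assume 9 independent scores with P(ES = 0) = 0.15 and P(ES = 1) = 0.10.

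- MCI as written: 1 − 0.85⁹ − 0.90⁹ + 0.75⁹ = 1 − 0.2316 − 0.3874 + 0.0751 = 0.456.
- Missed (n0 ≥ 2, n1 = 0): 0.90⁹ − 0.75⁹ − 9 × 0.15 × 0.75⁸ = 0.3874 − 0.0751 − 0.1352 = 0.177.
- Minimum severity: 0.456 + 0.177 = 0.633.
- Share of qualifying patients missed: 0.177 / 0.633 = 28%.

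**4. Correlated scores, by simulation.** The inputs are assumptions, except that ES = 0 is set at the bottom 5% of norms as in section 2.3:

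- 7 tests or 9 scores. Section 2.3 lists MoCA, RAVLT, Short Story, Visual Search, Stroop, fluency and sentence construction. RAVLT and Stroop give two scores each, which makes 9.
- Normal scores with inter-test correlation 0.3 or 0.5.
- ES = 1 as the next 5 or 10 centiles.
- The same mean deficit on every test.

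Share missed = 1 − P(MCI as written) / P(minimum severity). The ranges run over correlation and band width.

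| Mean deficit | MCI as written, 7 | Share missed, 7 | MCI as written, 9 | Share missed, 9 |
|---|---|---|---|---|
| 0 SD | 11–16% | 7–25% | 15–21% | 5–21% |
| 1 SD | 43–62% | 11–27% | 52–71% | 7–21% |
| 1.5 SD | 54–75% | 16–32% | 63–83% | 10–24% |
| 2.5 SD | 39–54% | 46–60% | 46–61% | 39–54% |

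Example (7 scores, correlation 0.3, 5-centile band, 1 SD): 1 − 0.469 / 0.644 = 27%.

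At deficits of 0 to 1 SD the share missed is therefore about 5–27% of qualifying patients, or 1 to 18 percentage points of all patients. At 2.5 SD, 98–100% meet the minimum-severity reading. The share labelled MCI as written is then lower than at 1.5 SD.

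**5. The two sections side by side.** Section 2.3 codes normal, borderline and abnormal. Section 2.7 describes performance as "evaluated as normal or abnormal by means of national normative data". If the second coding were used for the endpoint, n1 could not be counted.

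**The case against.** The best defence is that the sentence states a minimum: on an ordinal scale, a requirement of at least a 0 and a 1 can be taken to be exceeded by two 0s. The text does not say that several pathological scores rule MCI out, and the study team may never have meant that. This is a fair account of the likely intent, and it makes the point a wording defect. It does not remove the defect, because the second element names a specific value and nothing lets a lower one satisfy it.

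A second defence is that severely impaired patients may be diagnosed with dementia, which section 2.7 also counts. Some will be. But that diagnosis also draws on functional status, so it does not clearly catch functionally intact patients with several pathological scores.

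Third, the wording in section 2.7 may be a loose summary that leaves the three levels in place. That is possible, so the passages need to be reconciled; they do not prove that the borderline level was dropped.

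A reader might also infer more than the document supports:

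- *Decline is coded as improvement.* A patient who goes from 0, 1 to 0, 0 does lose the label under the literal rule. But section 2.7 has no improvement category for cognition. This patient had MCI at baseline and would not be a new MCI case under the reworded rule either.
- *Associations between markers and cognition are biased towards zero.* The check contains no marker and no change over time, so neither direction nor size has been shown.
- *About half of affected patients are missed.* That needs a deficit of about 2.5 SD on every test. Nothing in the article supports this for outpatients able to give consent. From 0 to 1 SD the literal rule still rises with severity.
- *Patients with MCI at baseline are wrongly left at risk.* Occurrence already suggests a new diagnosis, and an article may leave the at-risk set to the full protocol.

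**Conclusion.** The point holds as a defect in the stated rule. Followed literally, the rule excludes every profile with two or more pathological scores and no borderline one, while admitting milder profiles. That conclusion rests on the text alone.

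Its size rests on assumptions that the article does not supply: number of scores, correlation, width of the borderline band, and a uniform deficit. The range of about 5–27% at 0 to 1 SD is the more relevant one for this cohort, and 39–60% at 2.5 SD marks the extreme. A larger battery would lower the share: at 1.5 SD, correlation 0.3 and a 5-centile band it falls from 31% with 7 scores to 23% with 9. Section 2.3 names domains such as executive functions and speed that have no heading of their own in the test list, so there may be more than 9 scores.

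The mismatch between sections 2.3 and 2.7 is a smaller, separate inconsistency. Only the cognitive secondary endpoint, and MCI status at baseline, are affected. The primary endpoint of SVD progression on MRI is not.

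**What to change.** For the study endpoint, reword the rule in section 2.3 as at least one score of ES = 0 plus at least one further score of ES 0 or 1. In section 2.7, refer to the three-level coding of section 2.3 in place of the two-level description. Apply the reworded rule to both the baseline and the 18-month assessments.

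The cost is two sentences and a recode of equivalent scores already collected; follow-up was still under way when the article was written. The downside is that MCI prevalence rises somewhat: by 1 to 18 percentage points at mean deficits of 0 to 1 SD under the assumptions above. If MCI counts have already been produced under the literal rule, report both counts once so that the change can be seen.

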### 2.4. Cerebral Magnetic Resonance Imaging Assessment

Cerebral MRI scans were performed at baseline, and again 18 months after enrollment. The brain imaging protocol was planned and set up by imaging personnel with different expertise and skills, as suggested by current guidelines [25].

Baseline and follow-up MRI examinations are performed on an Ingenia 1.5-Tesla MRI unit (Philips Healthcare, Eindhoven, The Netherlands). Our standardized MRI protocol consisted of the following sequences: sagittal T1-weighted spin-echo (repetition time (TR) = 547 ms; echo time (TE) = 12 ms; slice thickness = 5 mm; interslice spacing = 0.5 mm; matrix size = 320 × 250; field of view (FOV) = 23 cm × 23 cm; number of signals averaged (NSA) = 1), coronal T2-weighted fast spin-echo (TR = 3347 ms; TE = 110 ms; slice thickness = 5 mm; interslice spacing = 0.5 mm; matrix size = 512 × 322; FOV = 22 cm × 22 cm; NSA = 2); axial fluid-attenuated inversion recovery (FLAIR) (TR = 11,000 ms; TE = 125 ms; inversion time (TI) = 2800 ms; slice thickness = 5 mm; interslice spacing = 0.5 mm; matrix size = 384 × 204; FOV = 23 cm × 23 cm; NSA = 2); axial gradient-echo T2* (GRE) (TR = 534 ms; TE = 23 ms; flip angle (FA) = 18; slice thickness = 5 mm; interslice spacing = 0.5 mm; matrix size = 256 × 185; FOV = 23 cm × 23 cm; NSA = 1); axial diffusion-weighted imaging (DWI) (TR = 3891 ms; TE = 75 ms; slice thickness = 5 mm; interslice spacing = 0.5 mm; matrix size = 164 × 162; FOV = 23 cm × 23 cm; NSA = 2); gradient-echo 3D T1-weighted (TR = 7.5 ms; TE = 3.4 ms; TI = 950, slice thickness = 1 mm; matrix size = 256 × 241; FOV = 25.6 cm × 25.6 cm; NSA = 1) followed by multiplanar reconstruction (MPR) in axial, coronal, and sagittal planes. DWI images were obtained by single-shot echo-planar spin-echo sequences according to the Stejskal–Tanner method. The diffusion gradients were applied in three orthogonal directions (*x*, *y*, *z*) with two b-values (0 and 1000 s/mm^2^) to form the isotropic DWI images at b 1000 s/mm^2^. Apparent diffusion coefficient (ADC) maps were generated automatically by the software provided by the manufacturer from isotropic DWI images and concurrent images with a b value of 0 s/mm^2^ by using the following equation: ADC = -ln [S(b)/S(0)]/b, where b indicates the b value and S(b) and S(0) are the signal intensities of images with b values equal to 1000 and 0, respectively.

Each MRI scan was evaluated by an expert neuroradiologist, and a written medical report was provided to patients. Neurologists involved in the project revised the report before returning it to patients, so that any incidental findings could be handled according to individual needs. 

Qualitative and quantitative analyses of SVD-related features on MRI are under way. 

The following features related to SVD will be assessed: i) lacunar infarcts, either silent or not; ii). white matter hyperintensities; iii) microbleeds; iv) dilated perivascular spaces; v) cortical and subcortical atrophy; vi) superficial siderosis [5].

Non-lacunar infarcts will be visually assessed in terms of number and location of lesions.

